## Discussion

As a result of the intervention, and per our sample size calculation, we anticipate that Black women within selected PPIL health centers will be more likely to receive PrEP prescriptions following implementation, contributing to an anticipated increase in PrEP uptake of up to 15 percent. This magnitude of impact would be statistically significant and clinically meaningful, supporting scale-up through PPIL and other family planning centers. The present study design is powered to detect small increases during the study period and will support future exploratory analyses to examine trends over time. During post-intervention analysis, we anticipate identification of important barriers and facilitators as a continuum during the implementation process at the patient, clinician, health center, and system levels.

As the duration of the intervention period will differ by health center due to the SW-CRT design, implementation outcomes will be assessed at various stages at the different study health centers. This variance will be a strength in analysis in that a wider variety of implementation experiences will be available to us; however, the health centers with the shortest intervention periods may provide somewhat limited evidence for measures such as implementation and maintenance. Throughout the study, we will monitor and evaluate procedure adaptations and modification as well as implementation processes at each health center; this support will include facilitating provider training, providing technical and logistical assistance such as EHR support, and serving as a resource for PrEP navigators and clinical champions. Additionally, we will measure the acceptability and fidelity of the intervention package to document strengths and weaknesses while determining the progress on achieving the primary and secondary clinical outcomes through regular analysis of EHR data.

Although the SW-CRT design is well-suited for this study due to its pragmatism and robustness, we also anticipate some design-related challenges will arise throughout the implementation process. In SW-CRTs, challenges such as structural limitations to adopt strategies may occur within the health centers. Additionally, changes to the planned timeline for the trial (lengthened or shortened duration), delayed or early implementation in clusters, or other logistical and technical issues (e.g., staff turnover, potential contamination across sites, health center resistance to intervention, loss of resources, etc.) can be significant challenges in SW-CRTs [29]. The randomization of health centers to various steps may also cause tension or frustration with partners due to health centers receiving the intervention at different times. To mitigate and address these potential challenges, we have incorporated a three-month transition period immediately preceding implementation of the strategies at each health center to ensure staff are prepared and have the necessary resources for implementation.

Additionally, the transition period serves as an opportunity to anticipate and prepare for any potential health center-specific challenges and to streamline implementation of PrEP uptake strategies, enabling a shift from standardized practices to increased comfort with utilizing the new systems and talking about PrEP among PPIL’s leaders, clinicians, staff, and patients. The one-year pre-implementation period will be utilized to build rapport and trust from health center staff to improve buy-in and develop relationships that will support implementation. For example, the pre-implementation processes will include the identification of at least one clinical champion to serve as a liaison between the health center staff and study team; the developed relationship with the clinical champion in particular will be leveraged to identify and address staff concerns or need for clarification or re-education and to gain on-the-ground knowledge to more effectively support centers throughout the duration of the study. Finally, any deviations and modifications to the study design and procedures will be documented in a tracking framework developed by the study team based on FRAME to help measure fidelity to the intervention [26].

By investigating effective implementation strategies for prevention of HIV infection among Black women, specifically in the EHE priority jurisdiction of Cook County, IL, the findings of this study will support women at increased need for HIV prevention using evidence-informed interventions. Understanding identified barriers and facilitators to the implementation and effectiveness of EUPHORIA could help improve not only PrEP delivery at local PPIL health centers but also understanding of similar interventions within other family planning centers and the larger Planned Parenthood Federation of America. Upon successful implementation, these data will inform the next steps, including to extend lessons learned within similar health centers to broaden reach and to scale up the intervention package. This study may also serve as a foundation for future studies of PrEP initiation and persistence in broader, more diverse settings. The findings of this study will be disseminated to participating health centers via written reports and presentations and to the larger community in the form of conference abstracts and publications in peer-reviewed journals in an effort to reduce the gap in PrEP delivery and uptake, share effective implementation strategies for use among a key population, address disparities in access to HIV prevention care, and contribute to the overall elimination of HIV transmission, especially among Black women.

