#### Sample size.

This study will be powered to determine whether there is a statistically significant difference in PrEP prescriptions among at-risk Black women defined as those with a positive STI test accessing family planning services between the intervention and control periods. We choose to use presenting to a family planning clinic and a positive STI test (gonorrhea, chlamydia, or syphilis) as eligibility to ensure patients at high risk for HIV acquisition are offered PrEP within the PPIL context, keeping in line with the CDC’s guidance to offer PrEP to patients at substantial risk of HIV acquisition. A power calculation was conducted based on a mixed effects effectiveness model with a random intercept for clinic and intervention and time as fixed effects. Assuming a baseline PrEP uptake of 1% and a conservative intraclass correlation coefficient (ICC) of 25%, a trial with 10 PrEP-eligible Black women per month (30 women per step) at each of the 8 clinics (8 steps) would allow us to detect an increase to 5% PrEP uptake (corresponding to an odds ratio of 5.21 for the intervention effect) in eligible Black women following the introduction of the intervention with >90% power at a two-sided alpha of 0.05. Our sample size provides almost 100% power for detecting a larger increase to 15% PrEP uptake (corresponding to an odds ratio of 17.47 for the intervention effect). Our sample size accounts for both the clustered nature of the design and the potential confounding effect of time. We used R software for power analysis.

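### The Discussion claims power for small increases, but the smallest effect the sample-size section powers is a rise from 1% to 5% (odds ratio 5.21)

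*Protocol article*

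**What the plan says.** In the protocol article, the Sample size section assumes a baseline uptake of 1%, an ICC of 25%, 30 eligible women per step at each of 8 clinics, and a mixed model with a random clinic intercept and fixed intervention and time effects. It says this "would allow us to detect an increase to 5% PrEP uptake (corresponding to an odds ratio of 5.21 for the intervention effect"), "with >90% power at a two-sided alpha of 0.05". It adds "almost 100% power for detecting a larger increase to 15% PrEP uptake", with an odds ratio of 17.47. No other effect size is powered anywhere in the article.

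The Discussion says "The present study design is powered to detect small increases during the study period". Just before that, it appeals to the sample-size calculation for the expectation that more women will receive prescriptions, "contributing to an anticipated increase in PrEP uptake of up to 15 percent".

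Two other sections bear on this. The Setting section puts current PrEP use among Black women below 1% at every site. The Study design section assigns each site a three-month transition period that counts in neither condition.

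**The concern.** The Discussion describes a sensitivity that the calculation does not show. A reader would take small increases to mean something near the 1% baseline, such as a doubling. The calculation starts at a five-fold rise. If the true effect were a doubling, most trials of this design would miss it, and the published statement would encourage reading the non-significant result as evidence against even a modest benefit.

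The 15 percent sentence adds to the blur. In the Sample size section 15% is the level reached, a rise of 14 percentage points, and it is an assumed alternative. A power calculation assumes an effect and cannot supply the expectation that it will occur.

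**Working it through.** **Inputs.** From Sample size: baseline 0.01, ICC 0.25, n = 30 per site and quarter, 8 sites, two-sided alpha 0.05. From Trial status: 27 months, so T = 9 quarters (one baseline quarter plus 8 steps). The ICC scale is not stated, nor whether 1% is a marginal rate or the rate at a typical site, so several variants are shown.

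**Odds ratios.** (0.05/0.95)/(0.01/0.99) = 5.21 and (0.15/0.85)/(0.01/0.99) = 17.47. Both match the article. A doubling is 2.02, a tripling 3.06, and 1% to 4% is 4.13.

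**Closed form** (Hussey-Hughes, random site intercept, fixed period effects):

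Var = Iσ²(σ² + Tτ²) / [(IU − W)σ² + (U² + ITU − TW − IV)τ²], power = Φ(Δ/SE − 1.96)

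Here I = 8, T = 9, U = 36, W = V = 204. So IU − W = 84, and the second coefficient is 1296 + 2592 − 1836 − 1632 = 420. Also σ² = p(1−p)/30 and τ² = (0.25/0.75)·p(1−p).

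**The plan's own figure first (1% to 5%).** With the average p = 0.03: σ² = 0.00097, τ² = 0.0097, Var = 0.000685/4.155 = 0.000165, SE = 0.01284, 0.04/SE = 3.115, power 88%. With arm-specific residual variance (generalised least squares on the same layout), SE = 0.01121 and power is 95%. The stated figure above 90% is therefore reproducible.

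**Smaller effects, same formulas.** 1% to 2%: average variance SE = 0.00915, 0.01/SE = 1.093, power Φ(−0.867) = 19%. 1% to 3%: SE = 0.01054, 0.02/SE = 1.898, power Φ(−0.062) = 48%.

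**Cross-check.** A logistic random-intercept model was simulated (600 runs per scenario, τ² = 1.097 from ICC 0.25 on the latent scale, Wald test).

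| Variant (power, %) | 1→2% | 1→3% | 1→4% | 1→5% |
|---|---|---|---|---|
| *No quarter dropped* | | | | |
| Closed form, average variance | 19 | 48 | 72 | 88 |
| Closed form, arm-specific variance | 20 | 53 | 81 | 95 |
| Closed form, baseline variance in both arms | 27 | 76 | 98 | 100 |
| Logistic, 1% at a typical site | 30 | 66 | not run | 95 |
| Logistic, 1% marginal | 22 | 46 | not run | 87 |
| *Transition quarter dropped* | | | | |
| Closed form, average variance | 15 | 36 | 57 | 74 |
| Closed form, arm-specific variance | 16 | 42 | 69 | 87 |
| Closed form, baseline variance in both arms | 20 | 61 | 92 | 99 |
| Logistic, 1% at a typical site | 25 | 53 | not run | 87 |
| Logistic, 1% marginal | 16 | 38 | not run | 75 |

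With a tenth quarter added to make room for the transition, the most generous variant gives 65% for a tripling, the top of the range quoted. The simulated test rejected 5-8.5% of the time under no effect, so the simulated powers are if anything optimistic.

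**A larger denominator (assumption).** Table 2 lists 224 + 438 + 224 + 144 + 502 + 518 + 217 + 144 = 2,411 Black women in 2023. Spread evenly over 8 sites and 4 quarters, that is 2,411/32 = about 75 per site and quarter. Closed-form power is then 41-56% for a doubling and 85-99% for a tripling, or 30-42% and 71-94% with the transition quarter dropped.

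**The case against.** Small is not defined, and the phrase follows a mention of 15 percent. A rise of 4 percentage points could be called small in absolute terms. That reading is possible, so this is a loose claim and not a numerical contradiction. Still, the article expresses the same effect as an odds ratio of 5.21 on a 1% baseline, and saying 4 points would cost one phrase.

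The article's arithmetic is not at fault: both odds ratios are right and the power above 90% reproduces.

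Three stronger readings are tempting, and the documents do not support them.

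- A reader might infer that the trial would usually be non-significant after a tripling. The two variants closest to the stated power give 53% and 66%, so a tripling is underpowered but not usually missed. It falls below 50% only in some variants, mostly those with the transition quarter dropped.
- A reader might infer that nothing short of a five-fold rise is powered. With arm-specific variance and no quarter dropped, 1% to 4% reaches 81%.
- A reader might infer that the design could never have this sensitivity. The figure of 30 per step belongs to STI-positive women, while Table 3 and the implementation-phase section describe a broader eligible population. At about 75 per site and quarter, a tripling could be adequately powered. A doubling still would not be.

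The 15 percent wording is minor, since the phrase is hedged as an upper limit and differs from the powered rise by one point. How a non-significant result will be interpreted is commonly left to an analysis plan, so its absence here is no fault.

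**Conclusion.** The point holds as a misstatement of sensitivity. The smallest effect the article powers is 1% to 5%. On its stated inputs, power is about 19-30% for a doubling and 46-76% for a tripling, or about 15-25% and 36-65% with the transition quarter excluded. Both stay below 80% in every variant. With arm-specific variance and no quarter dropped, about 80% is first reached near 1% to 4%.

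These figures rest on 30 women per site and quarter, nine quarters (ten only for the 65%), and an ICC of 0.25 whose scale is not given. The conclusion for a doubling also survives the larger denominator. The conclusion for a tripling does not necessarily do so. No design, model or decision rule is affected.

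**What to change.** In the Discussion, replace the claim about small increases with the effect the calculation supports: a rise from 1% to 5%, odds ratio 5.21. Beside it, report the power for 1% to 2% and for 1% to 3%, stating the ICC scale, the denominator and whether transition quarters are excluded. Reword the 15 percent sentence as a rise to 15%, a scenario assumed in the power calculation and not an expectation derived from it.

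The cost is a few words and one extra line of output from the existing power program. The only downside is that the claimed sensitivity becomes less favourable.

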### Trial status

The study is registered under NCT06335121. The SW-CRT will take place over the course of 27 months, with implementation strategies being rolled out at one site every 3 months. The research team will modify procedures as needed to ensure successful implementation at each health center throughout the duration of the trial.
